### Laboratory procedures for baseline and follow-up visits

#### *Demographics and medical history*

During the baseline visit only, participant demographics recorded included: date of birth, sex, race and postal code. An interview was then conducted to determine medical history, which included documenting information regarding smoking status, alcohol consumption, history of heart/vascular disease, history of endocrine disease, gynecological history, lifestyle habits, past illnesses and surgeries, and current medications. While the full interview was conducted only at baseline, it was requested that participants contact the study coordinator should there be any change in any of these items and at each follow-up visit participants were asked if there was any change in medication or health status.

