### Statistical analysis

#### *Outcome measures*

Clinic systolic blood pressure was chosen as the primary outcome measure.

Secondary outcomes included other metabolic syndrome, clinical and novel cardiometabolic risk factors. Scores from behavioural and health status questionnaires were also included in secondary outcomes.

Tertiary outcomes were mobile health variables including biometrics, activity and compliance to the monitoring protocol.

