#### *Sample size calculation*

The sample size was based on differences in mean change between the intervention and active control groups in systolic blood pressure (primary outcome measure) at 12-weeks. The sample size calculation assumed 80% power and two-sided significance level of 0.05. We estimated that the smallest difference between groups in mean change that would be expected was 6 mmHg and we assumed a common standard deviation of 12 mmHg. Therefore, it was determined that 63 participants would be required per group. By assuming a 15% drop-out rate, this would increase our required sample size to 73 participants per group. Since we are using an Analysis of Covariance (ANCOVA) to perform data analysis (primary analysis), this sample size estimation may be considered conservative.

Data will be analysed following the Intent-to-Treat approach. Analyses will include all safety evaluable patients who have both baseline and valid post-baseline data. In instances where a participant may not have completed the final visit of the protocol but was subjected to the above procedures before study termination, a last observation carried forward approach will be used for analysis. Baseline data will not be carried forward.

For all continuous outcome variables, distributions will be examined to assess normality and presence of outliers; transformations will be undertaken as appropriate. For categorical outcome variables, frequency tables will be examined to ensure there are no out-of-range values.

Descriptive statistics will be computed for baseline demographic characteristics and for all outcome measures, at each time point. Specifically, means and standard deviations will be calculated for continuous variables and frequency counts and percentages will be calculated for categorical variables.

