#### *12-week analyses*

For all continuous outcomes, ANCOVA will be used to examine differences in mean change between and within groups, while adjusting for baseline levels of the outcome of interest. For categorical outcomes, binary variables will be derived and we will use logistic regression to model the odds of improvement in either the intervention or active control group, while adjusting for baseline levels of the outcome of interest.

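### The 12-week systolic ANCOVA names baseline pressure as its only covariate; prespecifying age, sex and blood pressure drug use as well would be a modest, cheap improvement

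*Protocol article*

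**What the plan says.** - **Outcome** (Outcome measures): "Clinic systolic blood pressure was chosen as the primary outcome measure".
- **Model** (12-week analyses): change in each continuous outcome is compared by ANCOVA "while adjusting for baseline levels of the outcome of interest". No other covariate is named. The sample size section identifies ANCOVA as the primary analysis.
- **Data held at V0** (Demographics and medical history): "participant demographics recorded included: date of birth, sex, race and postal code". The interview at the same visit also covers "past illnesses and surgeries, and current medications".
- **Allocation** (Recruitment and screening process): everyone seen in one week goes to intervention, everyone seen in the next to control, and so on. No stratification factor is given. Drugs that affect heart rate are an exclusion.
- **52-week models** (52-week analyses): mixed models with group, time and group-by-time terms. Baseline is one of the modelled time points and the group term carries the baseline difference, so baseline is a response there and not a covariate.
- **Interpretation** (52-week analyses): it rests mainly on estimates and 95% confidence intervals.

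**The concern.** Age (18 to 70 years at entry), sex and use of blood pressure drugs could plausibly predict systolic change even after baseline pressure is taken into account. They are already collected for everyone, and neither the allocation nor the stated model uses them. Two things are at stake in the 12-week difference.

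The first is precision: any variance these factors explain stays in the residual and widens the interval on which interpretation rests.

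The second is conditional balance: if the arms differ in these factors, the unadjusted part of that difference enters the estimate. This deserves more attention here than in a trial with individual concealed randomization. The arm follows from the appointment week, and consent is taken at the visit itself, so a difference between arms could be systematic as well as due to chance.

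**Working it through.** **1. The plan's own figure.** Inputs from the sample size section: "The sample size calculation assumed 80% power and two-sided significance level of 0.05"; "the smallest difference between groups in mean change that would be expected was 6 mmHg"; "we assumed a common standard deviation of 12 mmHg".

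n per group = 2 × (1.960 + 0.842)² × 12² / 6² = 2 × 7.849 × 4 = 62.8, rounded up to 63. This matches the plan: "it was determined that 63 participants would be required per group". Power at 63 per group is 80.1%, the standard error is 12 × √(2/63) = 2.14 mmHg, and the 95% half-width is 1.96 × 2.138 = 4.19 mmHg. No covariate gain enters this calculation.

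**2. Gain from the three added covariates.** Let R² be the share of residual variance they explain. The article gives none, so 2%, 5% and 10% are assumed. Residual SD = 12 × √(1 − R²); equivalent sample = 1/(1 − R²).

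| R² (assumed) | SD | Equivalent sample | n per group for 80% | Power at 63 | 95% half-width |
|---|---|---|---|---|---|
| 0 | 12.00 | 1.00 | 63 | 80.1% | 4.19 |
| 0.02 | 11.88 | 1.02 | 62 | 80.9% | 4.15 |
| 0.05 | 11.70 | 1.05 | 60 | 82.1% | 4.08 |
| 0.10 | 11.38 | 1.11 | 57 | 84.1% | 3.98 |

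**3. The starting SD.** The 12 mmHg is the SD assumed for change, before any adjustment. With equal SDs at baseline and 12 weeks and correlation r between them (assumed), the SD after baseline adjustment is 12 × √((1 + r)/2): 9.67 for r = 0.3, 10.39 for 0.5 and 11.06 for 0.7. Power at 63 per group is then about 94%, 90% and 86%. The added covariates act on this smaller residual, so the mmHg gains in step 2 are upper limits. For r = 0.5 and R² = 0.10, SD goes from 10.39 to 10.39 × √0.90 = 9.86, and the half-width from 1.96 × 10.39 × 0.178 = 3.63 to 3.44 mmHg. The equivalent-sample ratios do not change.

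**4. Price of three coefficients.** With N = 126 analysed, residual degrees of freedom go from 123 to 120. Under random allocation, k covariates multiply the expected variance of the difference by about 1 + k/(N − k − 3). That is 123/122 for k = 1 and 123/119 for k = 4, a ratio of 122/119 = 1.025. The net variance ratio is 0.98 × 1.025 = 1.005, 0.95 × 1.025 = 0.974 and 0.90 × 1.025 = 0.923. After this price the net gain is about nil, 3% and 8%.

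**5. Imbalance.** If the covariate score differs between arms by d SDs, the estimate shifts by d × √R² × 12. Under sound randomization the standard error of d is √(2/63) = 0.178.

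- One standard error: 0.178 × √0.02 × 12 = 0.30 mmHg, up to 0.178 × √0.10 × 12 = 0.68 mmHg.
- d = 0.5, less unlikely when whole weeks are allocated: 0.85 to 1.90 mmHg, or 14% to 32% of the 6 mmHg target.
- Drug-use example (both inputs assumed): a 15-point imbalance × 4 mmHg difference in change = 0.6 mmHg, which is 10% of the target and 0.6/2.14 = 0.28 of a standard error.

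Starting from 10.39 instead of 12, the shifts in the first two lines shrink by a factor of 0.87.

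**6. The mixed models.** A main effect of age, sex or drug use adds the same amount to a person's baseline and follow-up values. It therefore cancels from the change over time, exactly with complete data and nearly so otherwise. Only covariate-by-time terms would alter the group-by-time contrast.

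**The case against.** The strongest reply is that this is preference. ANCOVA on the baseline value is a standard, valid primary model and already holds what is usually the best single predictor of systolic change. There is no stratification factor that the model must carry. Under sound randomization, chance imbalance in other covariates is not bias and is already reflected in the standard error. The sizing takes no credit for covariates and is described as conservative. The gain rests on assumed values and is small, and excluding drugs that affect heart rate narrows the medication variation. All of this stands. It limits the point to an improvement.

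It could also be said that a condensed article may leave covariates to an analysis plan that is not shown. That applies to further sensitivity models. It applies less to the primary model, whose covariate the article does state: the proposal changes a stated choice and does not fill a gap.

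Three stronger readings may tempt a reader, and the documents support none of them:

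- *The primary estimate is biased, or the trial is underpowered, without these terms.* The 63 per group reproduces with no covariate gain, and no actual imbalance is reported.
- *The 52-week models share the same baseline-only adjustment and need the same terms.* The article models baseline as a time point there, and added main effects would leave the change contrast essentially untouched.
- *Adjustment repairs the week-based allocation.* It can address only recorded factors. Unmeasured differences and any clustering by week remain.

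**Conclusion.** The point holds as a minor, worthwhile improvement to the 12-week systolic analysis. The stated model is valid and the stated power does not depend on changing it.

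For an assumed R² of 2% to 10%, the added covariates are worth about 2% to 11% more participants, or roughly nil to 8% after the price of three coefficients. The precision argument alone is therefore weak at the low end of the range. Protection against imbalance carries more weight because whole weeks are allocated in turn. A half-SD imbalance in the covariate score would move the estimate by up to about 0.9 to 1.9 mmHg against a 6 mmHg target, but both that imbalance and R² are assumptions.

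**What to change.** In the 12-week section, state before the data are analysed that the systolic blood pressure ANCOVA adjusts for baseline systolic pressure, age (continuous), sex and blood pressure drug use at V0 (yes/no). Report the baseline-only ANCOVA as a sensitivity analysis.

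Limit the change to this outcome. A blood pressure drug term has no evident rationale for outcomes such as lipids or SF-36 scores, and in the logistic models extra covariates would also change the odds ratio being estimated. Leave the 52-week models as they are unless covariate-by-time terms are deliberately prespecified.

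The cost is one sentence and three degrees of freedom (123 to 120 with 126 analysed). No new data are needed, although recorded medications must be coded yes/no for blood pressure drugs, without reference to outcome. The report should say that this adjustment offsets imbalance from the week-based allocation only in part.

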#### *52-week analyses*

The 12-week analyses will be extended to include data collected at all time-points. Linear mixed models will be used for continuous outcomes. Within these models, the group variable will indicate differences between groups at baseline, the time variable will indicate change over time in the reference (i.e., active control) group, and the group × time variable will indicate whether change over time differs between groups. Contrast statements will be used to determine change over time in the intervention group.

A similar approach will be followed for categorical variables; however, generalized linear (logistic) mixed models will be used instead. Interpretation of study results will be primarily based on estimation and associated 95% confidence intervals [40]. Analyses will be performed using R 3.0.1 [41].

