Access to healthcare is often reduced in rural compared to urban communities. For example, Huron County in rural southwestern Ontario has a 27.5% physician vacancy rate (number of positions available for general practitioners) compared to 0% vacancy rate in nearby urban centres [20]. Innovative technologies including mobile health monitoring have the potential to increase access to healthcare. Our group completed a pilot study testing the feasibility and utility of deploying a mobile health technology kit for self-management of metabolic syndrome risk factors and physical activity in a rural population [21,22]. Twenty-four participants aged 30-72 years monitored their blood pressure three times per week and blood glucose two times per day with Bluetooth™ enabled devices paired with a smartphone. Additionally, pedometer steps were manually inputted daily and body weight was inputted weekly [21,22]. A health monitoring system including an application on the smartphone and a secure online database was used to transmit and store data [21]. Alarms were triggered when measurements were outside of pre-determined limits. Following the eight-week intervention, waist circumference, diastolic blood pressure and total cholesterol were reduced, physical activity and fitness were increased [22], and autonomic function was improved [23]. Furthermore, participants reported that the technology assisted in adopting new practices to improve wellbeing and did not take too much time or interfere with activities of daily living [21]. This study, however, could not conclude whether the mobile health protocol had added benefit to the exercise prescription.

Therefore, the purpose of this trial was to investigate the effects of a mobile health supported exercise prescription, compared to exercise prescription alone on metabolic syndrome and other global cardiometabolic risk factors in individuals at risk for cardiovascular disease and type 2 diabetes. It was hypothesized that the primary outcome, systolic blood pressure, and secondary outcomes would be improved in both groups, but to a greater extent in the mobile health intervention group at 12 weeks and that these changes would be better maintained at 24 and 52 weeks in the intervention group with mobile health support compared with the active control group.

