#### *Recruitment and screening process*

This study was approved by the University of Western Ontario Research Ethics Board (Protocol #15828). Community-dwelling adults aged 18-70 years were recruited via newspaper or radio advertisement, flyers, referral from healthcare professional and word of mouth. Interested candidates contacted the study coordinator for telephone screening. Participants were eligible if they had two or more metabolic syndrome risk factors according to National Cholesterol Education Program Adult Treatment Panel III criteria: waist circumference ≥ 88 cm (women) or ≥ 102 cm (men); systolic blood pressure ≥ 135 mmHg and/or diastolic blood pressure ≥ 85 mmHg; fasting plasma glucose ≥ 6.1 mmol/L; triglycerides ≥ 1.7 mmol/L; and high density lipoprotein cholesterol ≤ 1.29 mmol/L (women) or ≤ 1.02 mmol/L (men) [24]. Exclusion criteria were: systolic blood pressure > 180 mmHg and/or diastolic blood pressure > 110 mmHg; type 1 diabetes; history of myocardial infarction, angioplasty, coronary artery bypass or cerebrovascular ischemia/stroke; symptomatic congestive heart failure; atrial flutter; unstable angina; unstable pulmonary disease; use of medications known to affect heart rate; second or third degree heart block; history of alcoholism, drug abuse or other emotional cognitive or psychiatric problems; pacemaker; unstable metabolic disease and orthopedic or rheumatologic problems that could impair the ability to exercise. Participants who passed the initial screening were booked for a V0 appointment. To facilitate scheduling of group mobile health technology training sessions, block randomization was used, such that all participants attending appointments during week one were allocated to the intervention group and all participants attending appointments during week two were allocated to the control group and so on.

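### The 52-week mixed model drops the baseline adjustment used at 12 weeks and so loses precision at 24 and 52 weeks

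*Protocol article*

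**What the plan says.** All references are to the protocol article.

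- **12-week analyses.** Continuous outcomes are analysed by ANCOVA on change, "while adjusting for baseline levels of the outcome of interest". The Sample size calculation section names ANCOVA as the primary analysis and calls the sample size conservative for that reason.
- **52-week analyses.** The 12-week analyses are to be extended to all time-points with linear mixed models. The terms are spelled out: "the group variable will indicate differences between groups at baseline, the time variable will indicate change over time in the reference" (active control) group, and group × time shows whether change differs between groups. Contrast statements are named for change over time within the intervention group. Interpretation rests mainly on estimates and 95% confidence intervals.
- **Background.** Beyond a larger improvement at 12 weeks, the hypothesis is that "these changes would be better maintained at 24 and 52 weeks in the intervention group".
- **Sample size calculation.** "The sample size calculation assumed 80% power and two-sided significance level of 0.05". The "smallest difference between groups in mean change that would be expected was 6 mmHg and we assumed a common standard deviation of 12 mmHg". On that basis "it was determined that 63 participants would be required per group".

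**The concern.** A model whose group term is the baseline difference has the baseline visit in its outcome vector. As described, baseline is neither a covariate nor held equal between groups. The 52-week model is therefore not an extension of the ANCOVA: it replaces a baseline-adjusted contrast with a plain difference in change. At stake is the width of the 24- and 52-week intervals, on which the article says interpretation will rest, for every continuous outcome. A lesser consequence is that the trial will produce a second 12-week systolic blood pressure estimate that does not agree with the ANCOVA.

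**Working it through.** **Inputs from the article.** Two-sided alpha 0.05, power 80%, difference 6 mmHg, SD 12 mmHg (read as the SD of change), 63 per group, visits at 0, 12, 24 and 52 weeks.

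**Assumed, not in the article.** Correlation r between baseline and a follow-up visit of 0.3 to 0.8; equal variance s² at each visit; complete data.

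**1. The plan's own figure.** n = 2 × (1.96 + 0.8416)² × 12² / 6² = 62.8, so 63 per group. This reproduces the stated number. The formula uses the SD of unadjusted change, so the unadjusted contrast has the planned power (80.1% by the normal approximation).

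**2. What group × time estimates.** With time as a factor and complete data, the 12-week group × time coefficient equals the raw difference in mean change. In 150 simulated trials (r = 0.5, 63 per group) the two agreed to within rounding error (3 × 10⁻¹³).

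**3. Precision.** The variance of change is 2s²(1 − r). The variance after baseline adjustment is s²(1 − r²). Their ratio, adjusted to unadjusted, is (1 + r)/2, so the unadjusted interval is wider by the factor √(2/(1 + r)). This factor does not depend on n or the SD, so it applies at 24 and 52 weeks with r taken for that visit. For scale, here it is with the design SD and 63 per group, where the unadjusted SE is 12 × √(2/63) = 2.14 mmHg:

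| r | adjusted SE (mmHg) | unadjusted interval wider by | power for 6 mmHg, adjusted |
|---|---|---|---|
| 0.3 | 1.72 | 24% | 93.6% |
| 0.5 | 1.85 | 15% | 90.0% |
| 0.7 | 1.97 | 8.5% | 86.1% |
| 0.8 | 2.03 | 5% | 84.1% |

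The simulation at r = 0.5 gave mean SEs of 1.84 (ANCOVA) and 2.13 (mixed model).

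**4. The second 12-week estimate.** Let D0 and D1 be the group differences at baseline and week 12, and b the ANCOVA baseline slope. The mixed model gives D1 − D0 and the ANCOVA gives D1 − b·D0, so they differ in size by (1 − b) × D0. With b = r, the SD of this over chance imbalance is (1 − r) × s × √(2/63). At r = 0.5, s = 12 and the SD is 0.5 × 12 × 0.178 = 1.07 mmHg (simulation 1.12). The range is 1.26 at r = 0.3 to 0.68 at r = 0.8. A 3 mmHg baseline gap at r = 0.5 moves the estimate by 1.5 mmHg.

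**5. Only if time were linear.** The visit weeks have mean 22, deviations −22, −10, 2 and 30, and sum of squares 1,488. For a true group difference of 0, −6, −6, −6 mmHg, the slope is −6 × (−10 + 2 + 30)/1,488 = −0.0887 per week. The slope-implied change is −1.06 at week 12 and −4.61 at week 52, and the intercept is −4.5 + 0.0887 × 22 = −2.55, a baseline difference that does not exist. Under compound symmetry the slope test has 62% power for this pattern, against 83% for a three-degree-of-freedom test with time as a factor.

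**The case against.** Three stronger readings are tempting, and the article does not support them.

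- **That the primary result is left open between two estimates.** It is not. The Sample size calculation section names ANCOVA as primary, and the 12-week section specifies it. That a longitudinal model gives a somewhat different 12-week coefficient is ordinary.
- **That the model is a straight line and cannot test maintenance.** The article does not give the coding of time, and an article may leave that to the full plan. Discrete visits and a group term said to be the baseline difference fit a factor with baseline as reference at least as well. Group × time then gives between-group differences in change at 24 and 52 weeks directly. Even under linear time, a maintained effect would be distorted and tested with less power rather than necessarily missed, and the ANCOVA would still test the early effect.
- **That baseline data are wasted or the trial underpowered.** Group × time uses baseline through change, and the sample size was computed for unadjusted change, so the planned 80% is kept. What goes is the margin behind the claim of conservatism.

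A further objection is that the gain in step 3 presumes random allocation, whereas "all participants attending appointments during week one were allocated to the intervention group" and the next week's to control. Under such a scheme the two estimators can diverge systematically, and neither is automatically right. That stands as a limit on the size of the gain. It does not explain why the plan adjusts for baseline at 12 weeks and not afterwards.

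**Conclusion.** The point holds as an inconsistency within the plan with a modest cost in precision. The 52-week model is called an extension of a baseline-adjusted analysis but, by its own definition of terms, is not baseline-adjusted. The cost falls on the secondary 24- and 52-week comparisons: intervals about 5% to 24% wider for assumed correlations of 0.8 down to 0.3, with equal visit variances and complete data. The duplicate 12-week estimate typically differs from the ANCOVA by about 1 mmHg, against a design difference of 6 mmHg. Validity under randomisation, planned power and the primary analysis are not in question. The distortion from linear time is conditional on a coding that the article does not state.

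**What to change.** For continuous outcomes, model the 12-, 24- and 52-week values with group, visit as a factor, group × visit, baseline value and baseline × visit. Because allocation went by alternating weeks, baseline as a covariate is safer than forcing equal baseline means.

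Report between-group contrasts at 24 and 52 weeks, and for change from week 12 to week 52. The last states the maintenance hypothesis directly. Baseline adjustment changes it little if the baseline slopes at the two visits are similar, so it is named for clarity rather than for precision.

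State that the 12-week ANCOVA governs the primary result, whatever the mixed model shows at that visit. Making visit a factor also removes the linear-time risk.

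The cost is wording and a few degrees of freedom. No new data are needed. Nobody is lost from the analysis, since the article already limits it to participants with both baseline and valid post-baseline data.

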## Discussion

This study investigated the effects of an exercise prescription supported by mobile health technology compared to an exercise prescription alone to improve metabolic syndrome and global cardiometabolic risk factors in rural community-dwelling adults. It was hypothesized that the primary outcome systolic blood pressure would be reduced to a greater extent in the mobile health-supported intervention group at 12-weeks and that this improvement would be better maintained in the intervention group for the remainder of the year-long trial. Similar improvements in secondary clinical outcomes as well as more novel cardiometabolic risk parameters including autonomic and vascular function were expected.

Interventions aimed at preventing chronic disease are important in rural communities with increased cardiometabolic risk and reduced access to healthcare. This study included adults from a rural community with greater prevalence of obesity, diabetes and hypertension than the provincial average [42] and reduced access to healthcare compared to urban communities [20]. Thus, it was considered an ideal setting for an intervention leveraging novel mobile health technologies to promote increased physical activity to reduce cardiovascular risk.

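### The planned 24- and 52-week group effects are measured from baseline, so on their own they do not show whether the 12-week gain was better retained

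*Protocol article*

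**What the plan says.** The hypothesis at the end of the Background has two parts. The first is a greater improvement in the intervention arm at 12 weeks. The second reads: "these changes would be better maintained at 24 and 52 weeks in the intervention group with mobile health support compared with the active control group". The Discussion repeats this for systolic blood pressure: "this improvement would be better maintained in the intervention group for the remainder of the year-long trial". In both places, what is to be maintained is the improvement already seen at week 12. The word is not defined further.

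The section on 52-week analyses builds on the week-12 analysis: "The 12-week analyses will be extended to include data collected at all time-points". It then gives a meaning to each term of the linear mixed model. For group, "the group variable will indicate differences between groups at baseline". Time is the change in the control arm. For the interaction, "the group × time variable will indicate whether change over time differs between groups". One use of contrasts is named: "Contrast statements will be used to determine change over time in the intervention group". That is a within-arm quantity. No between-arm comparison starting at the 12-week visit (V1) is described, and the section does not say whether time enters as categories or as a linear trend.

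**The concern.** Once the group term is the baseline difference, the interaction can only be a difference in change since baseline (V0). An effect at week 24 or 52 then contains two things that the hypothesis treats separately: the initial 12-week gain, and what each arm kept or lost afterwards. A large early effect that is partly lost can still leave a difference in favour of mobile health at week 52. Equal losses in both arms leave the early difference intact. In neither case has the intervention arm lost less of its gain, yet the planned term points the same way as it would if it had.

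What is at stake is the second half of the stated hypothesis. The Abstract also lists keeping improvements over time among the matters the results will inform.

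**Working it through.** **Inputs from the Sample size calculation section.** Difference 6 mmHg in mean change at 12 weeks, SD 12 mmHg, 80% power, two-sided 5%, 15% drop-out, 63 per group rising to 73.

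**The plan's own figure.** n = 2 × (1.96 + 0.84)² × 12² / 6² = 62.7, so 63 per group; power at 63 is 80.1%. The stated 73 follows from 63 × 1.15 = 72.5. (63 / 0.85 would give 75, a difference that does not matter here.) The 63 reproduces. It concerns week 12 only, and the article gives no planning values for weeks 24 or 52.

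**Decomposition.** Let D(t) be the between-group difference in change from baseline at week t (intervention minus control; negative favours the intervention). With time as categories, D(t) is the interaction at week t, and

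D(52) = D(12) + [D(52) − D(12)].

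The bracket is the between-group V3−V1 contrast, that is, retention since week 12. V2−V1 is D(24) − D(12). The planned term reports the sum.

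**Illustrations.** All trajectories are assumed (mmHg change from baseline at weeks 12/24/52).

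| Case | Intervention | Control | D(12)/D(24)/D(52) | V2−V1 | V3−V1 |
|---|---|---|---|---|---|
| A | -8/-6/-4 | -2/-2/-2 | -6/-4/-2 | +2 | +4 |
| B | -12/-10/-8 | -4/-4/-4 | -8/-6/-4 | +2 | +4 |
| C | -10/-8/-6 | -4/-2/0 | -6/-6/-6 | 0 | 0 |
| D | -6/-6/-6 | -6/-3/0 | 0/-3/-6 | -3 | -6 |

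In A and B the signs are opposite. In C the planned term is -6 while absolute retention is equal. In D the two agree.

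**Precision.** Take SD 12 as the SD of change, with 63 per arm: SE = 12 × √(2/63) = 2.14. The chance of a significant result in favour is Φ(|D|/2.14 − 1.96).
- Case A: D(52) = -2, 95% CI -2 ± 4.2, or -6.2 to +2.2; chance about 15% (17% with 73 per arm).
- Case B: D(52) = -4; chance about 46% (52% with 73 per arm).

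For case B, a random-intercept model was simulated (63 per arm, assumed correlation 0.5, 120 runs). The week-52 interaction was significant in favour of the intervention in 48% of runs. V3−V1 averaged +4.1 and was significant against the intervention in 51%.

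**If time is linear.** For case A, the least-squares slope of the differences 0, -6, -4, -2 on weeks 0, 12, 24, 52 (mean 22) is [(-22)(0) + (-10)(-6) + (2)(-4) + (30)(-2)] / (484 + 100 + 4 + 900) = -8/1488 = -0.0054 mmHg per week, or -0.3 over 52 weeks. For B it is -1.8 over 52 weeks, and in the simulation it was significant in favour in only 7% of runs. A linear model also forces the change from week 12 to week 52 to be (52 − 12) = 40 times the same slope, so it cannot separate early gain from later loss.

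**The case against.** **Maintained can be read another way.** The changes in question are improvements from baseline, so better maintained could mean that a larger improvement is still present at weeks 24 and 52. The planned interaction estimates exactly that. This stands. A reader might infer that the second hypothesis has no estimate that answers it, but the article does not support that. It has one that answers this reading and does not isolate the other.

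**V3−V1 is not a neutral measure.** An arm that never improved has nothing to lose, and an arm with a larger gain has more. In case A the intervention arm is called worse on V3−V1 although its reduction at week 52 is still twice that of control (-4 against -2). In case C both arms lose 4 mmHg, so the contrast is 0, yet the intervention keeps 6/10 = 60% of its gain and control keeps none. This also stands. It rules out reserving the maintenance claim for V3−V1 alone, which would only exchange one debatable choice for another.

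**A wrong claim is not inevitable.** Interpretation is to rest on estimates with 95% intervals. In case A that interval is inconclusive, and with linear time the slope shows almost nothing. Case B needs a week-12 difference of 8 mmHg, above the 6 mmHg planned for. Nothing in the article says that a week-52 coefficient alone will be reported as better maintenance. A reader might infer that the plan will label the arm that loses more as the better one; the article shows only that the planned term could not rule this out.

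**It is detail for a fuller document.** An article need not list every contrast, the V1-based ones can be derived from a categorical-time model, and means at each visit are promised. This goes only part of the way. The section is not silent: it states what each term will mean and which contrast will be used, and that interpretation does not separate the two parts of the hypothesis.

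**Conclusion.** The point holds in a limited form. The article hypothesises better maintenance of the 12-week improvement, but the between-group term it interprets over 52 weeks is referenced to baseline. That term combines initial gain with later loss and does not on its own show whether the gain was better retained. Under assumed trajectories the two quantities can have opposite signs: -2 against +4 mmHg, or -4 against +4 mmHg.

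The structural part rests only on the stated definition of the group term. The sizes rest on assumed trajectories, on SD 12 applying to later changes, and, for the simulation, on a correlation of 0.5. The sample size and the primary 12-week ANCOVA are unaffected.

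**What to change.** In the section on 52-week analyses:

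1. State that time is fitted as categories.
2. Add two between-group contrasts from the same mixed model, each with a 95% confidence interval: V2−V1 and V3−V1, intervention minus control.
3. Report them beside the baseline-referenced differences at weeks 24 and 52.
4. Define the conclusion. Better maintenance requires both a between-group difference still present at week 52 and no greater loss since week 12 in the intervention arm, judged from the two intervals together.

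The cost is two contrast statements and a few lines of text; no new data are needed. There are three drawbacks to state. The V3−V1 interval may be wide: with SE 2.14, if the change since week 12 also has SD 12, an estimate of +4 has an interval of about -0.2 to 8.2. An arm with a larger initial gain has more to lose. And the last-observation-carried-forward rule in the Sample size calculation section sets V3−V1 to zero for anyone who leaves after V1, which counts them as having kept their 12-week change in full, so the contrast should be read with the number of such participants in each arm.
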